### Outcomes

The primary outcome is weight change from baseline. Secondary outcomes are (1) body mass index (BMI) and fat mass change from baseline; (2) lipid and glycemic profile change from baseline (total cholesterol, LDL-cholesterol, HDL-cholesterol, triglycerides, fasting glucose); and (3) fecal microbiota profile and short-chain fatty acids (SCFAs) change from baseline. Body weight will be measured as a unique and established quantitative primary outcome, while assessment of body composition, biochemical profile, and gut microbiota will provide information on the cardiometabolic status of participants. The metric used will be the change in mean values from the beginning to the end of each dietary intervention.

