### Statistical analysis

Statistical analyses will be performed using SPSS software for Macintosh (SPSS Inc., Chicago, IL, USA). Data will be analyzed using intention-to-treat and on-treat procedures. The primary outcome (change in body weight) will be analyzed within each group using Student’s *t*-test for paired data. The difference in absolute change (mean value at baseline subtracted from the mean value after the intervention for each subject) will be estimated using the Student’s *t*-test for independent data. Evaluation of distributions and checking for outliers will be performed using histograms and box plots. If appropriate, variables will be logarithmized to normalize the distributions of data. Continuous variables that follow a normal distribution will be summarized using the mean and standard deviations. Categorical variables will be presented in terms of frequencies and percentages. After testing the regression assumption, a general linear model for repeated measurements with adjustments for possible confounding factors will be run to compare the effects of different interventions. Data for the general linear model will be reported as geometric means and 95% confidence intervals. The same analyses will be performed for secondary outcomes. Subgroup analyses will be performed to analyze possible differences in the changes, according to some characteristics of the study population, such as age and gender.

Before starting the data analysis, the level and possible causes of missing data will be investigate using appropriate tables. This information will be used to determine whether the level and type of missing data have the potential to introduce bias into analysis results or substantially reduce the precision of the estimates for the proposed statistical methods. Sensitivity analyses will be performed, based on the assumption that the missing outcomes are the worst or best possible in the different randomization groups. If these show that the conclusions may differ based on the missing values, further multiple imputation will be performed for the missing values. These analyses will consider the results of any losses at follow-up to the extent that they relate to differences in the measured variables (i.e., under the assumption of random missingness). A *P* value < 0.05 will be considered statistically significant.

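### The body-weight analysis and an unadjusted 0.05 threshold are carried over without exception to the fecal microbiota profile, whose sequencing data they do not suit

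*Protocol article*

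**What the plan says.** The Outcomes section of the protocol article lists, as the third group of secondary outcomes, "fecal microbiota profile and short-chain fatty acids (SCFAs) change from baseline". It then gives one metric without separating the outcomes: "The metric used will be the change in mean values from the beginning to the end of each dietary intervention".

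The Statistical analysis section describes the analysis of body weight. The change "will be analyzed within each group using Student’s *t*-test for paired data", and the difference between arms "will be estimated using the Student’s *t*-test for independent data". Distributions and outliers are inspected, and "If appropriate, variables will be logarithmized to normalize the distributions of data". In addition, "a general linear model for repeated measurements with adjustments for possible confounding factors will be run", with results given as geometric means and 95% confidence intervals. The section then says "The same analyses will be performed for secondary outcomes", and closes with a single threshold: a P "value < 0.05 will be considered statistically significant".

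The Data collection and management section says where the microbiota profile comes from: amplicon sequencing of 16S regions for bacteria and ITS for fungi. It also names six short-chain fatty acids. The article does not give the number of taxa, the taxonomic level, or whether taxa are tested singly or reduced to summary measures.

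**The concern.** The carry-over sentence fixes a method for the microbiota profile, and that method was built for one continuous, always positive measurement. Sequencing output differs in three ways.

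- **Zeros.** Many taxa are absent from many samples. The log transformation is the only remedy that the section offers for skewed data, and the geometric mean is its reporting scale for the model. Neither exists at zero.
- **Closure.** Abundances are shares of a fixed total. If one dominant taxon truly rises, the shares of the others must fall, so taxa whose absolute amounts are unchanged can test as changed.
- **Number of features.** A t-test on a profile can only be run feature by feature or on a summary index. Run feature by feature at 0.05, it produces false positives in proportion to the number of features. It also gives no test of the overall profile, which is the named outcome.

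Within-group paired tests add a further difficulty. Both diets are hypocaloric, so either arm may show a change that says nothing about chronotype timing.

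Gut microbiota is in the trial's title and in the objective at the end of the Introduction, and the Discussion looks to it for therapeutic targets. Unadjusted taxon-level findings would feed directly into those claims.

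**Working it through.** The plan gives no figure of its own on this point, so there is none to reproduce.

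**Inputs from the protocol article.** The level per test is 0.05, with no adjustment named (Statistical analysis). The individually named secondary variables other than the microbiota are BMI and fat mass (2), lipid and glycemic markers (5, Outcomes) and short-chain fatty acids (6, Data collection and management): 2 + 5 + 6 = 13. The planned total is 150, allocated 1:1, with 22% loss assumed (Sample size): 75 × 0.78 = 58.5, so about 58 completers per arm.

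**Inputs assumed.** The number m of null taxa, because none is given; tests taken as two-sided, because sidedness is not stated.

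**Step 1: chance findings among taxa.** The expected number of false positives is 0.05 × m, whatever the correlation between taxa. If the tests were independent, the chance of at least one is 1 − 0.95^m.

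| m (assumed) | Expected false positives | Chance of at least one, if independent |
|---|---|---|
| 10 | 0.5 | 40% |
| 20 | 1.0 | 64% |
| 50 | 2.5 | 92% |
| 100 | 5.0 | 99.4% |
| 200 | 10.0 | >99.9% |

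These figures are for one between-arm test per taxon. The paired tests within each arm come on top.

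**Step 2: closure.** A simulation used 100 taxa, 58 participants per arm, one dominant taxon with a base weight of about 20%, 20,000 reads per sample and 300 replicates, all assumed except the arm size. Only the dominant taxon was allowed to change, and only in one arm. The independent t-test on change was applied to the other 99 taxa, on raw shares and on logs. The logs needed 0.5 added to each count, a device the protocol does not mention. The expected number by chance is 99 × 0.05 = 4.95.

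| True change in the dominant taxon | Significant among 99 unchanged, raw | Same, log |
|---|---|---|
| None | 4.3 | 5.5 |
| 2-fold | 5.8 | 9.6 |
| 4-fold | 13.9 | 33.1 |

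With no shift, error per taxon is near nominal. Once one taxon truly shifts, closure adds false findings beyond chance, and the log transformation makes this worse.

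**Step 3: the other secondary variables.** With 13 variables and no true effect, 13 × 0.05 = 0.65 false positives are expected. Under independence the chance of at least one is 1 − 0.95^13 = 0.487, about 49%. That is a ceiling. The Data collection and management section defines BMI as weight over height squared, so in adults its change nearly duplicates the primary outcome. Total and LDL cholesterol are likewise related. Correlation leaves the 0.65 as it is and lowers the 49%.

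**The case against.** The strongest reply is that this is one generic sentence in an article that condenses a fuller protocol. Zero handling, compositional transformation, community-level tests and false-discovery control are commonly left to an analysis plan, and their absence alone is no fault. That is right as to absence. The sentence, however, does not leave the method open: it prescribes the body-weight analysis for every secondary outcome. An analysis plan that used a compositional method would depart from it.

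A second reply is that taxon-by-taxon testing is nowhere stated. The profile might be reduced to a few diversity indices or phyla, for which t-tests are not inherently unsuitable. This stands, and it limits the multiplicity figure. A reader might infer that the trial will almost certainly report significant microbial changes even if the diet does nothing. The documents do not support that: it needs taxon-level testing, about 50 or more null taxa before several false positives are expected (2.5 / 0.05 = 50), and probabilities computed as if taxa were independent.

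Third, a reader might call the t-tests simply invalid. The simulation does not bear this out when nothing shifts, since per-taxon error is then close to nominal. The carried-over package also includes distribution checks and an adjusted model, so it is more than bare t-tests, although neither element deals with closure or multiplicity.

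Fourth, for BMI, fat mass, lipids, glucose and short-chain fatty acids the tests are acceptable in form. Body weight is the single primary outcome, and unadjusted supportive secondary analyses are common. Whether to correct across those 13 variables is a matter of preference. The 49% should not be read as the trial's actual error rate.

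**Conclusion.** The point holds for the microbiota profile. The protocol states a rule that extends the body-weight analysis and an unadjusted 0.05 to 16S and ITS sequencing data without exception, and the rule suits those data poorly. That logs and geometric means fail at zero counts needs only the presence of zeros. That the overall profile goes untested follows if features are tested singly. The distortion from closure depends on a true shift in some dominant taxon; its size in the simulation (13.9 or 33.1 of 99 unchanged taxa at a 4-fold rise) rests on the assumed set-up. The number of chance findings is 0.05 × m and depends on an m that the documents do not give: 1 at 20 taxa, 2.5 at 50, 5 at 100, 10 at 200.

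For the 13 other secondary variables only the labelling is at issue: 0.65 false positives expected under the global null, and at most about 49% for at least one. The primary outcome is not affected, so this should be corrected but does not threaten the trial's main conclusion.

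**What to change.** Exempt the microbiota profile from the carry-over sentence and give it its own short paragraph:

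- compare the arms, not the two time points within each arm, with a baseline-adjusted log-ratio (compositional) method and a stated rule for zeros;
- add one overall community-level test, such as PERMANOVA;
- state the taxonomic level and control the false discovery rate at 5% across taxa.

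For BMI, fat mass, lipids, glucose and short-chain fatty acids, keep the t-test or linear model. Label the results supportive, and report between-arm differences with 95% confidence intervals.

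The cost is wording and free software beside SPSS. Recruitment, visits and sampling do not change. The downside is fewer nominally significant secondary results.

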We hypothesize that aligning dietary patterns with the individual inherent biological clock will optimize metabolic processes and promote beneficial changes in gut microbial composition, ultimately leading to improved health outcomes. We also speculate that a chronotype-adapted diet may have a lower dropout rate because these diets are more easily adapted to each patient’s preferences.

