### Sample size

The calculation of the sample size and statistical power was measured considering the 80% probability to show as statistically significant (*p* < 0.05) a 1.4% weight reduction difference between the intervention group and the control group, with a standard deviation of 0.4% and a loss at follow-up of 22%. This calculation was derived from a study in the literature that evaluated the difference between a diet adapted to the chronotype and a control diet in overweight/obese subjects [16]. The minimum number of subjects to be recruited to obtain reliable results with a statistical power of 0.8 (beta) and 0.05 (alpha) is 54 participants per group. Dropouts will be included in the intention-to-treat analysis, which includes all participants initially randomized. Per-protocol analyses, focusing on those who complete the trial without major deviations, will also be conducted to provide a comprehensive perspective on treatment efficacy.

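### The declared intention-to-treat analysis has no final weight for dropouts, so the primary t-test is a completer analysis; imputation is a conditional add-on, triggered by undefined bounds that tell little at 22% loss

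*Protocol article*

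**What the plan says.** The Sample size section of the protocol article commits to intention-to-treat: "Dropouts will be included in the intention-to-treat analysis, which includes all participants initially randomized". It plans for 22% loss to follow-up.

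Three other sections determine what data a dropout can supply:

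- **Participant timeline:** two clinical evaluations only, at Time 0 and Time 1.
- **Data collection and management:** participants who stop before the four-month evaluation have no further clinical or laboratory assessment. The reason for withdrawal is recorded.
- **Statistical analysis:** weight change is tested within arms by a paired t-test and between arms by an independent t-test on each participant's change. An adjusted general linear model for repeated measurements follows.

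On missing data, the Statistical analysis section first plans tables of the extent and causes of missingness. Then: "Sensitivity analyses will be performed, based on the assumption that the missing outcomes are the worst or best possible in the different randomization groups". Then: "If these show that the conclusions may differ based on the missing values, further multiple imputation will be performed for the missing values". The imputation assumes random missingness.

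The Introduction adds an expectation about dropout: "We also speculate that a chronotype-adapted diet may have a lower dropout rate".

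**The concern.** The intention-to-treat statement and the analysis do not fit together. A dropout has no Time 1 weight, hence no change score, and no section says how such a person enters the primary test. In its usual form, a two-time-point repeated-measures model also needs both weights.

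Multiple imputation is the only method named that could bring dropouts in at plausible values. It is reached only if the bounds disagree, and the text does not say whether it then replaces the t-test result or sits beside it. The trigger rests on values that have no natural meaning for weight change, so the analyst's later choice of fill value can decide whether imputation happens at all.

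At stake is whether the headline estimate covers all randomised participants or only those who stayed, and whether the sensitivity analyses can tell a reader how far to trust it. Between extreme bounds and missing at random, nothing is planned.

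**Working it through.** **1. The plan's own figure.** Inputs from Sample size: a difference of 1.4 points, SD 0.4%, 80% power, alpha 0.05 (two-sided assumed), 22% loss; stated result 54 per group.

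n = 2(1.96 + 0.84)² × (SD/difference)² = 15.7 × (0.4/1.4)² = 15.7 × 0.082 = 1.3, so 2 per group, or 3 after dividing by 0.78.

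The stated 54 is not reproduced. That is a separate matter, but it means 0.4% cannot serve to judge the bounds.

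**2. The SD implied by 54 per group (an assumption here).** Solve SD = 1.4 × √(n/15.7).

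- If 54 includes the loss: 54 × 0.78 = 42 completers, so SD = 1.4 × √(42/15.7) = 2.29.
- If 54 is before loss: SD = 1.4 × √(54/15.7) = 2.6 (2.57 from the exact t-test).

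**3. Numbers missing.** 150 participants at 1:1 is 75 per arm; 0.22 × 75 = 16.5, so 16 or 17 missing and about 58 completers per arm.

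**4. Width of the bounds.** Let f be the fraction missing, and fill dropouts at their own arm's mean ± k SD, in opposite directions by arm. Each arm mean moves by f·k·SD, so the difference moves by 2·f·k·SD each way, and the best-to-worst gap is 4·f·k·SD. With f = 17/75 = 0.227, SD 2.29 and a completer difference of 1.4:

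- k = 2: shift 2 × 0.227 × 2 × 2.29 = 2.08; worst case 1.4 − 2.08 = −0.68, best case 3.48, gap 4.2.
- k = 1: shift 1.04; worst case 0.36, best case 2.44, gap 2.1.

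At SD 2.57 the gaps are 4.7 and 2.3. Fills at the pooled minimum and maximum gave about 5.6 to 6.4 in simulation at that SD. The design difference is 1.4.

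**5. How often the conclusions differ.** Simulated normal changes, SD 2.29, 75 per arm, 17 missing per arm, missingness unrelated to outcome, 4,000 trials per cell. Each entry is the percentage of trials in which the completer, worst-case and best-case tests do not all agree in significance and direction.

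| Fill rule (assumed; the protocol gives none) | True difference 0 | 1.4 | 2.8 |
|---|---|---|---|
| Pooled observed min/max | 100 | 100 | 100 |
| Own-arm min/max | 100 | 100 | 83 |
| Own-arm mean ± 2 SD | 100 | 100 | 64 |
| Own-arm mean ± 1 SD | 100 | 79 | 1 |

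Other settings:

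- Pooled mean ± 1 SD gives at least 99% at differences of 0 and 1.4, but about 32% at a difference of 3 with SD 2.57.
- At the stated SD of 0.4% and a difference of 1.4, own-arm fills never trigger imputation. Pooled min/max triggers it in about 16% of trials with 16 missing and 42% with 17.
- At SD 2.29 and a difference of 1.4, lower loss changes the picture: 14 to 73% at 5% loss and 28 to 99% at 10%, depending on the fill.

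**6. What the bounds reveal at the design effect.** With SD 2.29, 17 missing per arm and a true difference of 1.4, the completer test has about 90% power. Superiority survives the worst case in about 0% of trials with min/max or 2-SD fills and about 20% with own-arm 1-SD fills. The best case is significant in about 100%. A sound result and a fragile one would look much the same.

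**The case against.** The case on the other side has real content.

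- **The plan says dropouts are included.** It does, and a completer analysis is nowhere announced. But no method is given, and a t-test on change cannot use a missing change. This is an unresolved conflict, which taken literally leaves completers.
- **Missing data are not ignored.** The plan tabulates missingness, records withdrawal reasons and includes a crude departure from missing at random through the bounds. That stands, and it narrows the gap to moderate, plausible departures.
- **Fill values and imputation covariates belong in an analysis plan, which is not shown.** This is fair for the details. It does not cover the conditional structure, which the protocol itself fixes.

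A reader might also infer stronger points that the document does not support.

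- **That the trigger always fires.** It does not: larger effects, milder fills or lower loss bring the rate well down.
- **That a trigger which fires makes the result rest on completers.** The reverse holds, since firing leads to imputation. Reliance on completers comes from the missing final weights and the change-score test.
- **That the primary analysis is biased because dropout is expected to differ by arm.** The Introduction only speculates, the sample size uses a single loss rate, and unequal dropout alone does not bias a completer comparison. Dropout must also relate to weight change.
- **That dropout by arm must become a trial outcome.** That is a separate reporting point.

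**Conclusion.** The point holds in this form: the intention-to-treat commitment conflicts with the data collected on dropouts and with the primary test, and imputation is left to a data-dependent trigger whose inputs are undefined and whose status once triggered is open. The primary result may be biased if leaving the trial is related to weight change; the size and direction of any bias cannot be derived from the document.

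At 22% loss and a true difference of 0 or 1.4 points, the bounds disagree in at least 99% of simulated trials with min/max, 2-SD or pooled 1-SD fills. With own-arm 1-SD fills the figure is about 79% at 1.4. The gap is about 4 to 6 points for the extreme fills and about 2 for 1-SD fills, against a target of 1.4. These figures assume an SD of 2.3 to 2.6 points, which the protocol does not state, normal changes and equal loss per arm. The conflict over intention-to-treat depends on none of these assumptions.

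**What to change.** 1. **Primary analysis.** Name one missing-data method for the intention-to-treat comparison and apply it without a trigger. A suitable choice is multiple imputation by arm using baseline weight, sex, age and calorie tier. Keep the completer t-test as supportive.
2. **Sensitivity analysis.** With only baseline data to impute from, the primary estimate will lie close to a covariate-adjusted completer analysis, so step 1 alone tests little. Replace the worst-case and best-case step with delta-adjusted imputation: let dropouts lose progressively less weight than imputed, up to a return to baseline weight, in both arms and then in one arm at a time. Report the deficit at which the conclusion changes.

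The scale is easy to read. A deficit of δ in one arm moves the difference by f·δ. At f = 0.227, a 3-point deficit in the intervention arm alone takes 0.227 × 3 = 0.68 off the difference. The same deficit in both arms cancels when loss is equal, which is why the one-arm runs are needed.

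3. **Timing.** Write this down before outcome data are examined by arm.

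The cost is some extra analysis work and possibly a slightly wider confidence interval. No new data are needed.

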### Oversight and monitoring

Regular monitoring of this study will be conducted by both the research team and the local Institutional Review Board. Given the study’s limited objectives, short duration, and the low-risk nature of the intervention, the establishment of a Data Monitoring Committee and a Trial Steering Committee was deemed unnecessary. The research group, appointed by the principal investigator, comprises a study coordinator, two physicians, four nutritionists, and a biostatistician. The team will convene regularly, typically monthly, to comprehensively assess ongoing trial progress. This includes a thorough review of study advancements, recruitment rates (actual versus predicted), data quality and return rates, protocol amendments, and general research study matters. The principal investigator will oversee these meetings, developing the agenda and serving as the study’s primary contact. At the halfway point and conclusion of the study, the protocol team will furnish the local Institutional Review Board with a comprehensive monitoring report, encompassing a review of activities, progress, challenges, and any pertinent issues of concern.

Any changes to the protocol and information provided to participants will be submitted to the Ethics Committee for approval prior to implementation. No interim analysis will be conducted. Access to data will be limited to qualified personnel with unique password-protected accounts. Adverse events, such as unfavorable and undesirable signs, symptoms, abnormal laboratory results, or illnesses temporally associated with the intervention diet, will be collected from the time of randomization until the final 4-month follow-up visit for each participant, whether or not they are considered related to the intervention study. All adverse events will be followed up until their resolution.

